### Study protocol

After obtaining informed consent, patients will be randomized in a 1:1 fashion to group A, low-pressure pneumoperitoneum (8 mmHg) facilitated by deep neuromuscular blockade defined as a post tetanic count (PTC) of 1–2, or group B, normal-pressure pneumoperitoneum (12 mmHg) with moderate neuromuscular blockade defined as a train-of-four (TOF) count of 1–2. Randomization is supported by our statistician and will be performed by a randomization list created with Sealed Envelope [18]. Stratification by center and surgical technique (laparoscopic or robot assisted) will be used. Upon hospital admission and before surgery, patients will complete baseline questionnaires: the validated Dutch versions of the Quality of Recovery-40 [19] (QoR-40), McGill pain [20], and RAND-36 [21] questionnaires. In the participating hospitals, perioperative care is structured following the Enhanced Recovery After Surgery (ERAS) society guidelines for elective colorectal surgery [22, 23]. Adherence to the key elements of these guidelines will be scored for all patients.

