### Statistical methods and sample size calculation

The mean clinically important difference on the QoR-40 questionnaire as described by Myles et al. is 6.3 points on a scale of 40–200, with a standard deviation of 15 points [32]. In order to achieve 80% power to detect a 6.3 point difference with an *α* of 5%, a sample size of 89 patients per group is needed. Considering a 15% conversion rate to open surgery, 204 patients are required to secure 178 patients for the final analysis.

For the primary outcome analysis, factorial ANCOVA will be used to compare the QoR-40 score on postoperative day 1 for groups A and B and adjusted for covariates. For secondary outcome variables, a Student’s *t* test will be used to compare normally distributed variables, and a Mann-Whitney *U* test will be used for skewed variables. For categorical variables, a chi-square test will be performed. A *P* value of < 0.05 will be considered statistically significant. All analyses will be performed on an intention to treat base. For exploratory outcome measures, Bonferroni correction for capitalization on chance will be applied.

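### The 15% allowance is applied by multiplying by 1.15 instead of dividing by 0.85, so 204 randomised would leave about 173, not 178; the power effect is minor, and the intention-to-treat statement makes 178 the wrong count anyway

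*Protocol article*

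**What the plan says.** The protocol article, under Statistical methods and sample size calculation, takes a clinically important difference on the QoR-40 that "is 6.3 points on a scale of 40–200", "with a standard deviation of 15 points". For 80% power at an alpha of 5% it states that "a sample size of 89 patients per group is needed", which is 178 in total. It then inflates this number: "Considering a 15% conversion rate to open surgery", it says, "204 patients are required to secure 178 patients for the final analysis".

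The next paragraph of the same section plans a covariate-adjusted ANCOVA for the primary outcome and puts every analysis on an intention-to-treat footing. The target of 204 is repeated in the abstract and under Study population, but only this section justifies it.

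**The concern.** A rate of conversion is a share of the patients who are operated on. To have 178 left after losing 15%, one divides 178 by 0.85. The stated 204 looks like 178 multiplied by 1.15, which adds 15% of the wrong base and falls short.

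The number promised for the final analysis, and the power attached to it, would then not follow from the plan's own loss assumption. Anyone who later compares the analysed count with the planned 178 would be using a wrong benchmark. The sentence also treats conversions as patients who leave the analysis, which does not sit with intention to treat.

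**Working it through.** **Inputs** (protocol article, Statistical methods and sample size calculation, unless noted)
- Difference 6.3 points; SD 15; power 80%; alpha 5%.
- Allocation 1:1 (Study protocol section).
- Loss 15%; 204 randomised; 178 analysed.
- Sidedness is not stated. Two-sided is taken because it reproduces the plan's 89 per group; one-sided gives about 71.

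**1. Reproduce the plan's base figure**

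n per group = 2 × (1.95996 + 0.84162)² × 15² / 6.3² = 88.99, so 89 per group and 178 in total. This matches. It is the normal approximation; the t-test version gives 89.96, so 90 per group.

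**2. Reproduce the 204**
- Total: 178 × 1.15 = 204.7.
- Per group: 89 × 1.15 = 102.35, cut to 102, and 2 × 102 = 204.

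The 204 is therefore obtained by multiplying by 1.15 and rounding down. The plan does not show this step; it is inferred because it gives the printed number and division by 0.85 does not.

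**3. Check the three printed figures against each other**
- 15% lost from 204: 204 × 0.85 = 173.4, about 173 analysed.
- Randomised number that secures 178: 178 / 0.85 = 209.4, so 210 (105 per group).
- Loss at which 204 does secure 178: 1 − 178/204 = 12.7%.

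The gap is about 5 analysed patients (178 − 173.4 = 4.6) or 6 randomised patients (210 − 204).

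**4. Power at 6.3 points and SD 15, two-sided 5%, unadjusted**

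Normal approximation: power = Φ(6.3 / (15 × √(2/n)) − 1.96), with n per group. The t column uses the noncentral t distribution.

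| Analysed in total | n per group | Normal approximation | t test |
|---|---|---|---|
| 178 | 89 | 80.0% | 79.6% |
| 173.4 (204 less 15%) | 86.7 | 79.0% | 78.5% |
| 204 (converted patients kept) | 102 | 85.1% | 84.7% |

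For example, at n = 86.7: 15 × √(2/86.7) = 2.278; 6.3 / 2.278 = 2.765; 2.765 − 1.96 = 0.805; Φ(0.805) = 0.790.

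Within one method, the inflation error costs 80.0 − 79.0 = 1.0 point or 79.6 − 78.5 = 1.1 points. Setting the t figure of 78.5% against the nominal 80% would overstate the loss, because 178 itself gives 79.6% on the t basis.

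**5. Allowance for the planned ANCOVA (assumption)**

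The plan gives no correlation between the covariates and the outcome. With residual SD 15 × √(1 − r²), power at 173.4 analysed (normal approximation) is 79.0% at r = 0, 80.6% at r = 0.2, 82.6% at r = 0.3 and 89.1% at r = 0.5. The break-even follows from 1 − r² = 86.7/89, so r is about 0.16.

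**The case against.** A reader might infer from the shortfall that the design does not reach its stated 80% power. The case against that inference is strong, and most of it stands.

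- **Intention to treat.** Conversion happens during the operation, after randomisation, and does not in itself prevent a patient from completing the QoR-40 at 24 hours; the Outcome measures section even provides for help from a blinded nurse. Under the stated analysis principle, conversion alone removes nobody. With all 204 analysed, power is about 85%. Converted patients who stay in might dilute the difference, but the document gives no figure for this, so 85% is the value before any dilution.
- **ANCOVA.** The 89 per group rests on the unadjusted SD, while the primary analysis is adjusted. A weak correlation would recover the lost point. Baseline QoR-40 is collected, but the article does not name it as a covariate, so this gain is possible and cannot be credited with a number.
- **Size.** About 5 analysed patients and about 1 point of power would change no design decision.

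None of this rescues the sentence itself. If conversions are excluded, 178 should read about 173. If they are kept, the analysed number is 204 (with complete outcomes), and conversion is no reason to inflate. The stated 178 follows from neither reading. Condensation into a journal article does not explain it, because the 15%, the 204 and the 178 all stand in one sentence.

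**Conclusion.** The inflation is miscalculated: at the stated 15% loss, 204 randomised patients leave about 173, and 178 would need 210. Severity is minor. On the sample size paragraph's own premise (all conversions excluded, unadjusted comparison, 6.3 points, SD 15, two-sided 5%), power is about 79.0% by the normal approximation or 78.5% by t test, roughly 1 point below the matching value at 178.

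The documents do not support the stronger conclusion that the trial misses 80% power. That would require every converted patient to be dropped and the comparison to be unadjusted, and the same section says otherwise on both counts. What does need settling is the conflict between treating conversions as losses and analysing by intention to treat, because it decides which denominator applies.

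**What to change.** First reconcile the treatment of conversions with the intention-to-treat statement. Then restate the figures to match:

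- If converted patients are kept, drop conversion as the reason for inflating and give the power for 204 analysed: about 85% at 6.3 points and SD 15, before any dilution by conversions.
- If the margin up to 204 is meant as an allowance for missing primary outcomes, say so. State either that 204 tolerates a 12.7% loss while keeping 178, or that a 15% loss leaves about 173 with about 79% unadjusted power.

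The cost is one or two corrected sentences. No further patients need to be enrolled and the planned analysis does not change. Correcting the number to 173 or 210 without settling the analysis population would leave the contradiction in place.

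### QoR-40 at 72 h and 1 week is assigned to unadjusted two-sample tests, although baseline QoR-40 and the stratification factors are in hand and day 1 gets a covariate-adjusted ANCOVA

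*Protocol article*

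**What the plan says.** All statements are in the protocol article.

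- **Secondary analysis** (Statistical methods and sample size calculation): a Student's t "test will be used to compare normally distributed variables, and a Mann-Whitney" U test for skewed variables, and chi-square for categorical ones. No adjustment is mentioned.
- **Primary analysis** (same section): a factorial ANCOVA compares day-1 QoR-40 "for groups A and B and adjusted for covariates". The covariates are not listed.
- **Randomisation** (Study protocol): "Stratification by center and surgical technique (laparoscopic or robot assisted) will be used".
- **Baseline data** (Study protocol): before surgery "patients will complete baseline questionnaires", namely QoR-40, McGill pain and RAND-36. Table 2 also marks pain scores and PONV on the day before surgery.
- **Later QoR-40** (Outcome measures): the scores at 72 h and 1 week are listed as postoperative secondary outcomes.
- **Planning values** (Statistical methods and sample size calculation): a difference of "6.3 points on a scale of 40–200, with a standard deviation of 15 points".

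**The concern.** One instrument is measured in the same patients before surgery, at 24 h, at 72 h and at 1 week. The article adjusts for covariates at 24 h and then names tests with no adjustment for the two later times, without giving a reason. This is a method that the text states, not a detail left open. An SAP that followed it would carry the loss forward, and one that adjusted would depart from the published text.

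Three things are at stake:

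- **Precision.** Variation between patients that the baseline score could explain stays in the error term.
- **Calibration.** Stratified randomisation balances the arms within centre and technique. A test that ignores the strata uses a standard error that is somewhat too large.
- **Continuity.** The later scores show whether any early benefit lasts. If they are judged skewed, the Mann-Whitney test yields no difference in QoR-40 points to set beside the day-1 estimate or the 6.3-point threshold.

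**Working it through.** **Inputs from the article.** Difference 6.3 points, SD 15, power 80%, alpha 5%, 89 analysed per arm, 204 randomised (102 per arm at 1:1). These values size the day-1 outcome. Using them at 72 h and 1 week is an illustration, because the article gives no values for those times.

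**Assumed inputs.** The correlation r between baseline and later QoR-40, and the share R² of outcome variance explained by the strata. The article gives neither, so ranges are shown.

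**Step 1. Reproduce the plan's figure.** n per arm = 2 × (1.96 + 0.8416)² × 15² / 6.3² = 2 × 7.849 × 225 / 39.69 = 89.0. This matches "of 5%, a sample size of 89 patients per group is needed". The article does not state sidedness. Two-sided gives 89 and one-sided gives 71, so two-sided is used. The calculation is a plain two-sample one and takes no credit for baseline adjustment.

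**Step 2. Add the baseline score.** Residual SD = 15 × √(1 − r²). With m patients per arm, SE = SD × √(2/m), the 95% half-width is 1.96 × SE, and power = Φ(6.3/SE − 1.96).

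| r (assumed) | Residual SD | Variance reduction | Half-width, 89 per arm | Power, 89 per arm | Half-width, 102 per arm | Power, 102 per arm | n per arm for 80% |
|---|---|---|---|---|---|---|---|
| none (unadjusted) | 15.00 | 0% | 4.4 | 80% | 4.1 | 85% | 89 |
| 0.3 | 14.31 | 9% | 4.2 | 84% | 3.9 | 88% | 81 |
| 0.5 | 12.99 | 25% | 3.8 | 90% | 3.6 | 93% | 67 |
| 0.6 | 12.00 | 36% | 3.5 | 94% | 3.3 | 96% | 57 |

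Example at r = 0.5 and 89 per arm: SE = 12.99 × √(2/89) = 1.947; 6.3/1.947 − 1.96 = 1.275; Φ(1.275) = 90%.

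**Step 3. Ignore the strata.** If the arms are balanced within strata, the true SE of the arm difference is √(1 − R²) times the SE that the unadjusted test uses. The true two-sided alpha of a nominal 5% test is then 2 × [1 − Φ(1.96/√(1 − R²))].

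| R² (assumed) | 1.96/√(1 − R²) | True alpha |
|---|---|---|
| 2% | 1.980 | 4.8% |
| 5% | 2.011 | 4.4% |
| 10% | 2.066 | 3.9% |
| 20% | 2.191 | 2.8% |

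The error is always on the conservative side.

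**Step 4. Both together, by simulation.** The setting was 178 patients, six strata of assumed sizes (40, 16, 40, 16, 40, 26), blocks of 4 and 4,000 runs. With R² = 0.10 and r = 0.5, the t test had alpha 3.9% and power 81%. A main-effects ANCOVA on arm, baseline and strata had alpha 5.2% and power 93%. The formula agrees: residual SD = 15 × √(1 − 0.25 − 0.10) = 12.09, SE = 1.813, power = Φ(3.475 − 1.96) = 93.5%. The simulation error on a 5% rate is about √(0.05 × 0.95/4000) = 0.3 percentage points.

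**The case against.** The strongest case on the other side is that nothing here is invalid. Unadjusted comparisons in a randomised trial are unbiased, and chance baseline imbalance is already allowed for in their standard error. A t test and a main-effects ANCOVA both estimate the mean difference in QoR-40 points, so the day-1 and later results can still be compared unless the Mann-Whitney test is used. The article claims no power at 72 h or 1 week. The gain depends on a correlation that it does not give, and at r = 0.3 the half-width with 102 per arm moves only from 4.1 to 3.9 points. All of this stands. It limits the point to efficiency and consistency, but does not answer why a less precise method is fixed when the data for a better one are already collected.

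A reader might go further and infer that the primary factorial ANCOVA is itself mis-specified, or that it would lose power through small robot-assisted strata. The document does not support that. The wording on covariates is compatible with baseline QoR-40, centre and technique all being in the model, and a condensed article may leave the list to the SAP. No sentence describes arm-by-stratum interactions or equal weighting of strata, and no stratum sizes are given from which a power loss could be computed.

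The scope is also limited. Baseline adjustment cannot apply to outcomes with no value before surgery, such as the L-SRS, blood loss, complications or length of stay. McGill and RAND-36 at 3 months appear in Table 2 but not in the text's list of secondary outcomes, so it is not clear that the unadjusted tests were meant for them.

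**Conclusion.** The point holds for QoR-40 at 72 h and 1 week. The article fixes unadjusted tests there, although it collects the baseline score, stratifies the randomisation and adjusts the same scale at day 1. The consequence is lost precision and slightly conservative p-values, not bias or an inflated false-positive rate.

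The likely size is modest to moderate. With 89 per arm, SD 15 and a 6.3-point difference, power would be about 84% to 94% instead of 80% if the baseline correlation lies between 0.3 and 0.6. True alpha would be about 4.8% to 2.8% instead of 5% if the strata explain 2% to 20% of the variance. Both ranges are assumptions, and so is carrying the day-1 SD and difference over to the later times. At the low ends the gain is small. The direction does not depend on the exact values, provided that baseline or strata predict the outcome at all.

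**What to change.** - Analyse QoR-40 at 72 h and at 1 week with a main-effects ANCOVA on arm, baseline QoR-40, centre and technique. Alternatively, fit one repeated-measures model over 24 h, 72 h and 1 week with the same terms. Report the adjusted mean difference in points with its 95% confidence interval.
- If McGill and RAND-36 at 3 months are analysed, use the same model with each instrument's own baseline.
- If skewness is a worry, keep the rank test as a sensitivity analysis and not as a replacement for the estimate in points.
- Adjusted or stratified analysis of the remaining secondary outcomes is optional.

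The cost is a few sentences in the SAP, with a note that they replace the article's wording for these outcomes, and a few lines of code. Every variable is already collected.

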### Data management and monitoring

All patient data will be coded and stored anonymously in the certified cloud-based electronic data collection platform Castor [33]. A subject identification list is kept separate and securely stored in compliance with privacy legislation. Monitoring will be performed according to the negligible risk guidelines of the Dutch federation of academic medical centers [34]. A yearly progress and safety report will be submitted to the medical research ethics committee and competent authority.

## Discussion

One of the most rewarding collaborations between surgeons and anesthesiologists resulted in the development of the international evidence-based Enhanced Recovery After Surgery (ERAS) guidelines, introducing a cost-effective decrease in length of hospital stay and complications after surgery. The advantages vary between different types of surgery; however, the ERAS guideline for colorectal surgery is currently well established as the optimal standard of care [35]. Further optimization of surgical conditions requires a continued partnership in the operating room, where a promising advancement lies in the relationship between intra-abdominal pressure and the degree of muscle relaxation. There is extensive evidence to support that the pressure used to create a pneumoperitoneum during laparoscopic surgery is harmful to surrounding organs and structures. Insufflation pressures lead to compression of the capillary vasculature, causing ischemia-reperfusion injury and oxidative stress, especially during prolonged exposure [36–38]. Perfusion of the parietal peritoneum is significantly improved at low-pressure compared to standard pressure pneumoperitoneum (*Albers* et al.*, submitted*). Deep neuromuscular block reduces the pressure requirements and increases intra-abdominal volume, thereby increasing the available surgical workspace at a lower intra-abdominal pressure [39, 40]. Reducing intra-abdominal pressure without deep muscle relaxation compromises the surgical workspace and may not be safe, as illustrated by a higher incidence of surgical complications in patients with moderate neuromuscular block and low pressure pneumoperitoneum during our previous study in patients undergoing laparoscopic donor nephrectomy [9]. In addition, deep neuromuscular blockade in itself appears to be beneficial, leading to reduced postoperative pain scores and a decrease in opiate consumption independent of insufflation pressures [9, 41]. We confirmed these findings in our recently completed trial comparing moderate to deep neuromuscular block during laparoscopic surgery in living kidney donors [42]. Therefore, we hypothesize that the combined benefits of lower intra-abdominal pressure and deep neuromuscular blockade can further enhance quality of recovery after laparoscopic surgery.

Even though the beneficial effects of lower intra-abdominal pressure and deep neuromuscular blockade on surgical conditions are increasingly recognized for many laparoscopic procedures, the results on patient outcomes—especially for colorectal procedures—largely remain to be elucidated. The QoR-40 questionnaire provides a validated, reliable assessment of early quality of recovery [17]. The participating centers for this trial have been selected on satisfactory to exemplary compliance with the ERAS guidelines, Martini general hospital is one of the 24 ERAS centers of excellence worldwide [43]. This will allow us to determine whether low pressure pneumoperitoneum facilitated by deep neuromuscular blockade could be a valuable addition to the ERAS program. One of the main strengths of our study is that close registration of the perioperative parameters will allow for a reliable examination of the true effects of low pressure and deep neuromuscular blockade during colorectal laparoscopic surgery. A limitation of the study is that it will be performed in a single blinded manner; only the surgical team will be blinded. Blinding the anesthesiologist is not feasible as this would impair patient safety. After extensively weighing the costs and benefits, we chose not to blind the researcher in the operating room to improve adherence to the study protocol, especially regarding neuromuscular blockade. In our previous trials in living kidney donors, we have observed that achieving and maintaining adequate deep neuromuscular blockade throughout the whole surgery remains challenging. This resulted in cases with recurrent recovery to moderate or even shallow NMB during the procedure, disrupting the intended analysis. Currently, there are no clear guidelines concerning adequate dose and monitoring for a well maintained deep NMB. Moreover, there is a large variability in reported doses between trials aiming for a similar or equal block depth, and corresponding monitoring data is often lacking. By allowing the focus of one competent physician researcher on dosing and monitoring, we strive for less fluctuations and a representative intervention across all patients. To diminish the risk of bias, (post) operative outcome measures such as L-SRS scores, complications, and questionnaires will be registered and collected by a blinded member of the surgical team and blinded research nurse, respectively. Additionally, we strongly advocate the importance of developing a consensus guideline for deep neuromuscular blockade in future trials and use in clinical practice.

In conclusion, this multicenter randomized clinical trial will investigate the effect of low pressure PNP facilitated by deep NMB on quality of recovery after laparoscopic colorectal surgery. Moreover, the study will identify whether low pressure PNP and deep NMB could be a valuable addition to the ERAS guideline for colorectal surgery.

### Trial status

Protocol version 2—May 2018. Recruitment began in October 2018, and predicted completion of inclusion is in October 2020.

## Data Availability

All relevant data will be included in the article and its supplementary information files. Additional information is available from the corresponding author on reasonable request.

## Abbreviations

ANCOVA: Analysis of covariance
ERAS: Enhanced Recovery After Surgery
L-SRS: Leiden-Surgical Rating Scale
NMB: Neuromuscular blockade
NMBA: Neuromuscular blocking agent
OR: Operating room
PNP: Pneumoperitoneum
POD1: Postoperative day 1
PTC: Post tetanic count
TOF: Train of four
QoR-40: Quality of Recovery-40
SPIRIT: Standard Protocol Items: Recommendations for Interventional Trials
